The effect on postoperative cognitive performance in this patient population remains underinvestigated and is therefore not conclusively understood. Patients with a high intraoperative ONSD are more likely to appear disoriented during the awakening period or in the recovery room [19]. Due to the increasing use of RALP (80% of radical prostatectomies in the USA [20]), it is important to better investigate neurological complications and to develop a better monitoring strategy and awareness of potential transient brain damage. Some studies did not detect a cognitive deficit in patients after RALP [13]. Others, however, showed a lower outcome in standardized tests such as the mini-mental state examination (MMSE) in patients who experienced intraoperative IJV valve insufficiency [14]. Additionally, an increased risk of postoperative delirium was noted [21].

The correlation between postoperative (emergence) delirium and the observed intraoperative valve insufficiency suggests that an intraoperative fluid shift might occur leading to an endothelial dysfunction and reduced cerebral clearance, possibly resulting in transient neuronal damage. A very specific biomarker for neuronal damage that is increasingly gaining importance is the axonal protein neurofilament light chain (NfL) [22]. Previous work showed that NfL might serve as a prognostic marker not only in neuronal disease states but also in several other patient groups, e.g., after cardiac arrest [23,24] and cardiac surgery [25,26].

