## 2. Outcome Measures

### 2.1. Primary Endpoint

The primary endpoint of this study is the perioperative concentration of NfL in plasma (single-molecule array (SiMoA)).

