### 3.2. Timeline for Each Patient

After informed consent to participate in the study has been given, the baseline time point T0 will take place. On the day of the surgery, there are three time points scheduled: T1 after the induction of anesthesia, T2 1–2 h after incision, and T3 during emergence, after the patient has been repositioned. The follow-up period will consist of T4 on postoperative day one, T5 on postoperative day three, and T6 before discharge (usually postoperative days 5–7). An overview of the patients’ schedule of activities according to the standard protocol items—recommendations for interventional trials (SPIRIT)—is provided in Figure 1.

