### 3.6. Statistical Evaluation

The exact case number can only be approximated due to the lack of previous studies in this patient population. The obtained data from each patient will be analyzed individually. After testing for normal distribution (Kolmogorov–Smirnov test), the appropriate statistical test for comparison will be selected (e.g., repeated measurements ANOVA or Friedman test). The median, mean values, and standard deviations will then be calculated from the generated data sets of all patients. The data will be statistically analyzed using the software SPSS 24.0 (IBM, New York, NY, USA) and Sigma Plot 13 (Chicago, IL, USA). A significance level α of 0.05 and a statistical power of 0.8 were defined for this study. A flow chart of the trial is provided in Figure 2.

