### 3.8. Risk–Benefit Assessment

The study will require several study-specific measures on the patient. Some of them will be clinically necessary and most of the study-related measures will be non-invasive. The only invasive procedure will be the blood draw, where 20 mL will be drawn from each patient at seven time points (maximum total 140 mL). These blood draws will be carried out via existing catheters or as part of routine blood sampling where possible.

Each patient might already benefit directly through the monitoring of cognitive function. In both groups, occurring cognitive impairments (e.g., due to the choice of anesthetics) might be detected early and will be well documented. This will also lead to the introduction of countermeasures, which should, however, not affect the overall outcome of the study. Additionally, a better understanding of the adaptation in this particular position and a gain in knowledge regarding neuronal damage will be possible for the experimental group. This might contribute to an improvement in patient monitoring and safety. The easy-to-perform and non-invasive control of the ONSD [31] might be established as a standard monitoring tool within the department of anesthesiology and thus further improve the training of young colleagues.

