### 3.9. Data Management and Privacy

All data input, processing, and analysis will be carried out in accordance with the Data Protection Act. Only employees of the UroTreND Study will have access to all study data, and they are obliged to confidentiality. The data will be protected from unauthorized access. All patient-related data will be recorded in pseudonymized form (letter and number code): After signing the informed consent, each patient will be randomly assigned to an alphanumeric number of a defined number group. These alphanumeric numbers will then be encrypted together with the personal data.

Samples that are processed for this study will only contain the alphanumeric number and therefore will not provide any personal reference. A patient identification list including the full name, date of birth, and alphanumeric number will be maintained by the employees of this study, stored safely, and remain protected. This list will be necessary for decryption in case of medical or scientific reasons. Additional data from routine examinations or measurements will be added to the research database according to the alphanumeric pseudonymization. The patient identification list will be stored for up to 10 years after the conclusion of the trial. Each patient will be thoroughly informed about data management and privacy.

Patients will have the right to withdraw their consent and cancel their study participation at any time without being required to give any reasons. In such cases, the patient will be asked if they agree to the further use of their data/samples in an anonymized form, or if they prefer their data/samples to be deleted or destroyed.

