## 4. Analysis Methods

Blood samples will be taken at all time points T0–T6. The ONSD will be measured at T0–T4. Functional tests and questionnaires will be conducted at T0/T1 and T3–6 simultaneously for saliva collection. Urine samples will be taken, when possible, at T1 and T3/T4. The MRI scan will be performed at T0 and T4. An overview of the samples and procedures employed at each time point is provided in Figure 3.

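### The tests that section 3.6 gives as examples drop any patient with a missing value among the time points analysed, and Friedman cannot compare RALP with open surgery; a mixed model for NfL avoids both

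*Protocol article*

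**What the plan says.** The primary endpoint is in section 2.1: "The primary endpoint of this study is the perioperative concentration of NfL in plasma". No time point or contrast is attached to it. Section 4 states "Blood samples will be taken at all time points T0–T6", and section 3.8 agrees: "20 mL will be drawn from each patient at seven time points (maximum total 140 mL"). The last sample is "T6 before discharge (usually postoperative days 5–7") according to section 3.2.

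Section 3.5 plans 30 RALP and 20 open-surgery patients. It states a between-group hypothesis, namely higher postoperative NfL in the RALP group, and expects a rise from the preoperative measurement to the postoperative ones up to discharge.

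Section 3.6 sets out the analysis. A Kolmogorov–Smirnov test comes first, and then "the appropriate statistical test for comparison will be selected (e.g., repeated measurements ANOVA or Friedman test"). Alpha is 0.05 and power 0.8.

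**The concern.** The only methods mentioned are a parametric and a rank-based test for repeated measurements, and the only stated selection rule is distributional shape. Two properties make them a poor fit.

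- **Complete blocks.** In standard form each test needs a value from every patient at every time point entered. One missed tube removes the patient from all time points, including those where NfL was measured.
- **No group comparison in Friedman.** It ranks values within each patient across time. Run in each group, it shows whether NfL changes over time in that group. It does not test whether the change differs between RALP and open surgery. Repeated-measures ANOVA can do so if surgery is added as a between-patient factor.

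At stake are precision in a study of 50 patients and, if loss is related to NfL itself, some underestimation of the RALP difference.

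**Working it through.** **Inputs from the article.** 30 and 20 patients; up to 7 samples each; alpha 0.05; power 0.8. Not given: effect size, SD, sidedness and missing rate. The sample size therefore cannot be reproduced from a formula.

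**Back-solved reference.** For a two-sided comparison of two means, 30 versus 20 has 80% power at d = (1.960 + 0.842) × √(1/30 + 1/20) = 2.802 × 0.2887 = 0.809 SD. The 0.2887 is the standard error of the group difference in SD units. The value 0.809 serves only as a yardstick.

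**Complete-block behaviour.** In a simulated set of 20 patients by 7 times, one value was deleted. A repeated-measures ANOVA routine rejected the data as unbalanced. Friedman returned no result until the whole patient was removed. A mixed model kept all 20 patients and 20 × 7 − 1 = 139 values.

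**Complete cases.** Assume loss m per draw, independent between draws, over k draws at risk. The expected complete fraction is (1 − m)^k, and the standard error is multiplied by 1/√fraction. The last column is power at d = 0.809.

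| m (assumed) | Draws at risk | Fraction complete | Of 50 | SE factor | Power |
|---|---|---|---|---|---|
| 2% | all 7 | 0.98^7 = 0.868 | 43.4 | 1.07 | 74% |
| 5% | all 7 | 0.95^7 = 0.698 | 34.9 | 1.20 | 65% |
| 10% | all 7 | 0.90^7 = 0.478 | 23.9 | 1.45 | 49% |
| 2% | T4–T6 only | 0.98^3 = 0.941 | 47.1 | 1.03 | 78% |
| 5% | T4–T6 only | 0.95^3 = 0.857 | 42.9 | 1.08 | 74% |
| 10% | T4–T6 only | 0.90^3 = 0.729 | 36.5 | 1.17 | 67% |

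**Bias if loss is related to NfL.** These are large-sample simulations with unit SD and a true T6 difference of 0.80 SD. Loss follows a logistic function of the T4 or the T6 value.

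| Scenario | Missing, RALP / open | Complete-case difference | Likelihood-type estimate |
|---|---|---|---|
| Depends on observed T4; correlation 0.6, slope 0.5 | 13% / 11% | 0.79 | 0.80 |
| Depends on observed T4; correlation 0.6, slope 1.0 | 19% / 13% | 0.77 | 0.80 |
| Depends on observed T4; correlation 0.8, slope 1.0 | 13% / 7% | 0.76 | 0.80 |
| Depends on observed T4; correlation 0.8, slope 1.5 | 21% / 10% | 0.70 | 0.80 |
| Depends on T6 itself; correlation 0.6, slope 0.5 | 15% / 11% | 0.78 | 0.79 |
| Depends on T6 itself; correlation 0.6, slope 1.0 | 24% / 13% | 0.72 | 0.76 |

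The attenuation runs from 0.01 to 0.10 SD. Against the standard error of 0.289 SD, that is 0.01/0.289 = 0.03 to 0.10/0.289 = 0.35 standard errors. The likelihood-type estimate removes the bias when loss depends on observed values, and only part of it when loss depends on the unseen value.

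**The case against.** The strongest reply is that section 3.6 fixes nothing. The two tests follow an "e.g.", cover the data in general and are not assigned to NfL. An article may also leave missing-data handling to the full protocol or analysis plan. This stands against any claim that the plan commits to deleting patients. It does not help the methods that are named: both examples share the complete-block property, and a normality check does not lead to a method without it.

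A reader might infer stronger versions, which the article does not support:

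- **That every patient needs all seven samples.** No section says that T0–T6 enter one test. The requirement covers the time points analysed.
- **That draws depend on catheters or routine sampling.** Section 3.8 says "These blood draws will be carried out via existing catheters or as part of routine blood sampling where possible". That describes a way of taking the blood, and the same section plans seven draws per patient. It is not evidence of missed draws.
- **That a patient who declines the cognitive tests also stops giving blood.** Section 3.9 says only "Patients will have the right to withdraw their consent and cancel their study participation at any time", and then asks whether data and samples may still be used. Any partial-withdrawal option belongs to consent and protocol text that is not shown.
- **That the most affected patients will leave.** The Introduction says "Patients with a high intraoperative ONSD are more likely to appear disoriented during the awakening period or in the recovery room". That concerns the hours around emergence. No section links it to later withdrawal or to unequal loss by group.

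It is also fair that seven-draw independent loss is the harsh case. T1–T3 fall under anaesthesia or at emergence with venous lines in place, T6 precedes discharge, and withdrawal clusters a patient's misses. The T4–T6 rows are therefore the milder bound. Finally, a mixed model does not restore unmeasured values, so switching recovers only part of the precision lost.

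**Conclusion.** The point holds in a limited form. The comparisons that section 3.6 offers as examples exclude, in standard form, any patient with a missing value among the time points analysed, and one of them cannot test the trial's between-group hypothesis. A better-suited method is available at almost no cost.

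The size rests on assumed rates: about 43, 35 or 24 of 50 complete at 2%, 5% or 10% independent loss per draw over seven draws, or about 47, 43 or 36 if losses occur only at T4–T6. The attenuation, from 0.80 to about 0.70–0.79 SD, is conditional on loss being related to NfL. It is at most about a third of a standard error in these scenarios, and it concerns the ANOVA route only, because Friedman yields no RALP-versus-open estimate. The article documents neither a missing rate nor differential loss, so a bias in this trial is not shown.

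**What to change.** In section 3.6, name for NfL a linear mixed model on log NfL with group, time and group-by-time, and T0 as covariate. Fit it by likelihood to every available sample, including samples taken before withdrawal where the patient permits their use. The group and group-by-time terms give the RALP-minus-open difference at each time point, so neither the normality pre-test nor Friedman is needed for this endpoint.

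Add a sensitivity analysis for missingness that depends on unobserved NfL values, and report withdrawals and deleted data by arm.

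The cost is a few sentences of analysis text and some extra reporting, with no additional patients, visits or samples. There are three limits. The main model assumes that missingness depends on observed values. A patient without T0 cannot contribute when T0 is a covariate. Data that a patient asks to have deleted are lost under any method.

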### 3.7. Ethics and Good Clinical Practice

The trial will be conducted in accordance with the Clinical Trials Directive 2001/20/EC of the European Parliament and the Council of the EU, the International Conference on Harmonization guidance regarding Good Clinical Practice (ICH-GCP E6 R1), the relevant national regulations, and the Declaration of Helsinki. Ethical approval was obtained from the local Ethics Committee of the LMU Medical Faculty, Munich, Germany (protocol code 22-0562; 20 October 2022). Any modifications to the protocol will be immediately communicated to all responsible authorities. A completed SPIRIT checklist was provided as a Supplemental File of this manuscript (Figure S1).

### 3.8. Risk–Benefit Assessment

The study will require several study-specific measures on the patient. Some of them will be clinically necessary and most of the study-related measures will be non-invasive. The only invasive procedure will be the blood draw, where 20 mL will be drawn from each patient at seven time points (maximum total 140 mL). These blood draws will be carried out via existing catheters or as part of routine blood sampling where possible.

Each patient might already benefit directly through the monitoring of cognitive function. In both groups, occurring cognitive impairments (e.g., due to the choice of anesthetics) might be detected early and will be well documented. This will also lead to the introduction of countermeasures, which should, however, not affect the overall outcome of the study. Additionally, a better understanding of the adaptation in this particular position and a gain in knowledge regarding neuronal damage will be possible for the experimental group. This might contribute to an improvement in patient monitoring and safety. The easy-to-perform and non-invasive control of the ONSD [31] might be established as a standard monitoring tool within the department of anesthesiology and thus further improve the training of young colleagues.

### 3.9. Data Management and Privacy

All data input, processing, and analysis will be carried out in accordance with the Data Protection Act. Only employees of the UroTreND Study will have access to all study data, and they are obliged to confidentiality. The data will be protected from unauthorized access. All patient-related data will be recorded in pseudonymized form (letter and number code): After signing the informed consent, each patient will be randomly assigned to an alphanumeric number of a defined number group. These alphanumeric numbers will then be encrypted together with the personal data.

Samples that are processed for this study will only contain the alphanumeric number and therefore will not provide any personal reference. A patient identification list including the full name, date of birth, and alphanumeric number will be maintained by the employees of this study, stored safely, and remain protected. This list will be necessary for decryption in case of medical or scientific reasons. Additional data from routine examinations or measurements will be added to the research database according to the alphanumeric pseudonymization. The patient identification list will be stored for up to 10 years after the conclusion of the trial. Each patient will be thoroughly informed about data management and privacy.

Patients will have the right to withdraw their consent and cancel their study participation at any time without being required to give any reasons. In such cases, the patient will be asked if they agree to the further use of their data/samples in an anonymized form, or if they prefer their data/samples to be deleted or destroyed.

### 3.10. Quality Control and Assurance

The Department of Anesthesiology of the LMU University Hospital is certified according to the highest national standard qualification system that is also recognized globally (DIN-ISO-9001). This includes the quality management of clinical trials. All employees are specifically trained according to their tasks (e.g., data management and privacy, handling of measurement instruments). Simple plausibility checks are automatically carried out when entering new data. Furthermore, checks on the completeness of the data are regularly performed. This serves to identify and rectify quality defects at an early stage.

## 4. Analysis Methods

Blood samples will be taken at all time points T0–T6. The ONSD will be measured at T0–T4. Functional tests and questionnaires will be conducted at T0/T1 and T3–6 simultaneously for saliva collection. Urine samples will be taken, when possible, at T1 and T3/T4. The MRI scan will be performed at T0 and T4. An overview of the samples and procedures employed at each time point is provided in Figure 3.

### 4.1. Blood Processing

The concentration of NfL, as well as the concentrations of NSE, GFAP, Aβ40, and Aβ42, will be quantified by the highly sensitive SiMoA in EDTA plasma [32]. Matrix metalloproteinases-2 and -9, zonulin, S100B, hyaluronan, syndecan-1, and heparan sulfate will be measured with ELISA. Standard immune analyses such as differentials will be conducted at the Department of Clinical Chemistry at the LMU Hospital Munich. Functional analyses, leukocyte subsets, plasma cytokines, cell adhesion molecules, and markers of cellular activation will be evaluated using flow cytometry and multiplex assays on a Luminex^®^ xMAP^®^ platform (Merck Millipore, Darmstadt, Germany). The expression of signaling cascades of interest will be assessed facultatively via transcriptome (mRNA) and Western blot analyses. No genomic research (e.g., chromatin structure, mutations, single-nucleotide polymorphism) will be performed.

### 4.2. ONSD/Extracranial Blood Vessels

Focused sonography will be performed according to standardized operating procedures [31]: The optic nerve will be marked at a depth of 3 mm behind the retinal plane. At this depth, the transverse diameter will then be determined by a pair of measuring points, which are placed directly lateral to the reflex-rich cerebrospinal fluid space. As measurement inaccuracies cannot be ruled out, the measurement will be repeated three times, and the median value will be used. This procedure will be completed in under two minutes to avoid heat-induced eye damage [33]. In addition to the measurement of the ONSD, a screening of the extracranial cervical blood vessels will be performed (visual impairment of valve functionalities, flow changes).

### 4.3. Neurocognitive Tests

The functional tests are non-invasive and standardized.

MMSE: The MMSE is an established screening instrument for testing spatial orientation, memory, attention, numeracy, and language. To test orientation, ten questions are asked about time and place.Clock drawing test: The patient will be asked to write the numbers 1–12 and the time 11:10 in a provided circle on a sheet of paper. This very simple test is used to assess instruction comprehension, execution planning, and working memory [34]. It will be carried out in combination with the MMSE.The Nursing Delirium Screening Scale (NU-DESC) is an established screening test for delirium evaluation in under 3 min [35].Memory test: This test will be computer-based. The patient will be asked to memorize and reproduce a series of words (episodic memory) and numbers (digit span test). Additionally, the attention and reaction time is tested by clicking on a red button (red button task).

The test will contain the following parts:Learning of words with immediate recall;Red button task;Digit span forwards;Digit span backwards;Recall of words learned during part 1.

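### One fixed clock setting is repeated at five sittings, and one of the two tests named is purely within-patient, so practice could offset a cognitive decline or look like a time effect

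*Protocol article*

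**What the plan says.** Neurocognitive function (MMSE, clock drawing, Nu-DESC, memory test) is a secondary endpoint in section 2.2 of the protocol article.

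- **Clock (4.3).** One setting is given: "The patient will be asked to write the numbers 1–12 and the time 11:10 in a provided circle on a sheet of paper". On its pairing with the MMSE: "It will be carried out in combination with the MMSE".
- **MMSE (4.3).** The only item detail is "To test orientation, ten questions are asked about time and place". No version is named.
- **Memory test (4.3).** "The patient will be asked to memorize and reproduce a series of words (episodic memory) and numbers (digit span test". Whether the lists stay the same or change between sittings is not stated.
- **Schedule (4).** "Functional tests and questionnaires will be conducted at T0/T1 and T3–6 simultaneously for saliva collection".
- **Timing (3.2).** On the day of surgery: "T1 after the induction of anesthesia, T2 1–2 h after incision, and T3 during emergence, after the patient has been repositioned". T4 is postoperative day 1, T5 day 3, and T6 before discharge, usually days 5 to 7.
- **Analysis (3.6).** After a normality check, "the appropriate statistical test for comparison will be selected (e.g., repeated measurements ANOVA or Friedman test". No contrast is named for the cognitive scores.
- **Groups (3.5).** 30 RALP and 20 open-surgery patients. Section 4 gives one test schedule and does not separate the groups.

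**The concern.** A patient who has drawn the same clock several times within days may do better through familiarity alone. The same would hold for words and digits if they are reused. If the scores are read as change over time within patients, the observed change is the surgical effect plus the practice gain, and the two have opposite signs. A transient decline could then look smaller than it is. Where there is no decline, learning could produce a significant time effect that has nothing to do with surgery.

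The cognitive tests are the functional counterpart of the NfL hypothesis, and the introduction describes the existing evidence on cognition after RALP as conflicting. A null result, or a time effect, that partly reflects repeated testing would be hard to interpret. The content of the sittings cannot be changed once patients have been tested.

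**Working it through.** **1. Number of sittings.** Section 4 lists T0/T1, T3, T4, T5 and T6. T1 follows induction of anesthesia, so a cognitive test there is not feasible and baseline must be T0. That leaves five sittings. T3 to T6 run from the day of surgery to about days 5–7, so four of the five fall within about a week.

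**2. The plan's own figure.** The 30 + 20 patients were chosen with NfL in mind, and no effect size or SD is given for NfL or for any cognitive score. The number cannot be reproduced for cognition, and this point does not depend on it.

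**3. Within-patient reading.** Let *d* be the true decline and *g* the practice gain, both in units of the SD of the change score. Both are assumptions. The expected net fall is *d* − *g*. For a paired t-test in *n* = 30 RALP patients at two-sided 0.05, the noncentrality is (*d* − *g*)√30 and the critical value is 2.045 (29 df). For *d* = 0.5 and *g* = 0.2, this is 0.3 × 5.477 = 1.643, which gives 36%. The chance of a significant fall is:

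| Practice gain *g* | *d* = 0.5 | *d* = 0.8 |
|---|---|---|
| 0 | 75% | 99% |
| 0.1 | 56% | 96% |
| 0.2 | 36% | 89% |
| 0.3 | 18% | 75% |
| 0.4 | 8% | 56% |

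**4. Friedman over five sittings.** This was simulated with 30 patients, 2000 runs, between-patient SD 1, residual SD 0.7 and a gain of *g* score units at each further sitting (all assumed). The test rejects in:

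| Gain per sitting | No decline | Decline 0.5 at T3 and T4 |
|---|---|---|
| 0 | 5% | 87% |
| 0.1 | 35% | 98% |
| 0.2 | 94% | 100% |
| 0.3 | 100% | 100% |

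The overall test does not lose power under drift. It loses its meaning, because it rejects for learning alone as readily as for a decline.

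**5. Between-arm contrast.** The change in RALP is −*d*(RALP) + *g* and in open surgery −*d*(open) + *g*. The difference is −[*d*(RALP) − *d*(open)], so *g* drops out when it is equal in both arms. For a two-sample t-test on change (30 versus 20, 48 df), the noncentrality is Δ/√(1/20 + 1/30) = Δ/0.289. Power is 40% at Δ = 0.5, 53% at 0.6 and 78% at 0.8, whatever the size of *g*.

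This contrast is therefore less powerful than the paired test when practice is small. What it gains is that equal practice does not bias it, and that it addresses the comparison the study is built on.

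**The case against.** The strongest reply is that the trial has a concurrent control group on the same test schedule and a stated aim of comparing RALP with open surgery. Equal practice cancels in that comparison. The tests in 3.6 are only examples, repeated-measures ANOVA can carry a group-by-time term, and a fuller analysis plan may name it. This stands as far as it goes. However, the other example, Friedman, has no group term, and it is a plausible choice for bounded, ordinal scores once the normality check has been applied.

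It can also be said that the clock is the weakest case for learning, since the patient is told the time and need not recall it. That is fair, and it limits the likely size of the gain.

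A reader might infer more than the documents support:

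- *The whole battery has fixed content.* Only the clock setting is fixed. The text is silent on memory-test lists and MMSE versions, an article may leave these to the full protocol, and the MMSE time-orientation answers change with the date. The Nu-DESC is a delirium screen and this point does not concern it.
- *A decline is masked.* No practice gain or expected decline is given. With a large decline and a small gain little is lost, so this is a possible bias and not an established one.
- *Scores start at the ceiling because neurological and psychiatric disease are excluded.* No baseline scores are given. A ceiling would also leave less room for upward drift.
- *There are six or more sittings.* T1 is under anesthesia, so five is the supportable count.

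**Conclusion.** The point holds in a limited form. The article fixes one clock setting, schedules it at five sittings with four inside about a week, describes no alternate form for it, and offers a purely within-patient test as one of two examples. If cognition is read as change over time alone, practice may offset a postoperative decline or produce a spurious time effect.

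The size is unknown. Under assumed values, the chance of a significant fall in 30 RALP patients ranges from hardly affected (99% to 96% for a decline of 0.8 SD and a gain of 0.1 SD) to nearly lost (75% to 8% for a decline of 0.5 SD and a gain of 0.4 SD). These figures treat scores as normal and unbounded, which is a simplification. The between-arm contrast of change is free of this bias if practice is equal in both arms. That is plausible under a common schedule, but not guaranteed without randomization.

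This concerns one secondary endpoint in a study that calls itself a pilot. It is a worthwhile, cheap improvement and not a flaw that threatens the primary result.

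**What to change.** - **In 3.6**, state that the cognitive scores are compared as the RALP-versus-open difference in change from T0, and not as within-patient change alone. This can be the group-by-time term or, if scores are non-normal, a two-group comparison of change.
- **In 4.3**, vary the clock time across sittings. Confirm whether word lists, digit strings and MMSE recall words already change between sittings, and use parallel versions if they do not. Apply the same rotation in both arms.

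The cost is one sentence on the contrast and the preparation of a few alternative versions before testing starts. Versions may differ slightly in difficulty, but the common rotation balances that between arms.
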